**Table Tabb:** 

Identified needs of the population	Matched elements of the protocol
Bilateral movement	Warm up exercises Castanet playing Simultaneous bilateral piano playing
Finger isolation	Warm up exercises Multiple piano exercises (5-finger scales, 3-note arpeggios, Hanon-type exercises)
Finger strength	Use of a weighted keyboard or piano Resistance of castanets
Crossing midline	Use of full key range for distal and midline crossing
Range of motion	Transfer exercises (2c) Use of full key range for gross motor range of motion
Functional transfer	Object transfer task Improvisation piano task for self-cued movement without the motor learning element
Entrainment (for TIMP-RHY only)	Tempo assessment and use of metronome

The TIMP-NR research protocol uses musical instruments only as movement endpoints to provide auditory feedback for facilitating functional movement patterns [23]. The TIMP-RHY research protocol adds to the TIMP-NR an accompaniment with auditory rhythmic cues (via a metronome) to provide the critical feedforward information that creates anticipation, repetition, periodic stability (each cycle length consistent), and continuous time referencing to optimize trajectory, velocity, and acceleration (how much time has elapsed, how much time is left during the movement). On the first TIMP-RHY therapeutic session, a baseline tempo for the TIMP exercise (4a-d) will be assessed for each participant using a metronome. Then, the baseline tempo will be increased by 5% each week up to 180 bpm. Full TIMP-NR and TIMP-RHY research protocols are available for reference in the Supplementary documents section. Importantly, TIMP-RHY relies on external cueing for movement generation whereas TIMP-NR requires internally generated movements. Of note, patterned sensory enhancement (PSE), another sensorimotor rehabilitation NMT technique, is briefly utilized in the TIMP-RHY protocol and uses “musical patterns to assemble single, discrete motions (e.g., arm and hand movements during reaching and grasping), into functional movement patterns and sequences” [23]. Information regarding these techniques is available at NMTAcademy.co.
*(ii). Standard of care OT*: Participants who are randomized into the OT group will receive standard of care OT sessions, as prescribed by the patient’s primary neurologist. Research participants will work with one of the certified occupational therapists on our team, who all have expertise in PD and/or other neurological disorders. The occupational therapists will provide care 3 times per week for 5 consecutive weeks using the OT research protocol to provide a standard of care control matched for time with music therapist (full OT research protocol available in the Supplementary documents). Occupational therapists have robust experience in neurological recovery and are well versed in neurological re-education after the onset of a neurological injury. By incorporating their background knowledge on how the basal ganglia and proprioceptive tracks influence movement and how that movement impacts functional abilities, each individual’s engagement in this research study will be facilitated and monitored. Occupational therapists use functional activities and the use of daily self-care tasks and occupations to improve performance and independence in each individual’s unique daily roles (home, community, work and/or school). Therefore, the OT protocol was developed focusing on aerobic, proprioceptive, and coordination skills required to succeed in any daily routine.

In the case of any missed intervention session, the assigned therapist and the clinical coordinator will be in contact with the participant to schedule a make-up session, which will also help ensuring trial adherence.

No protocol discontinuation or modification is expected, as delineated in our protocol and consent form.

Concomitant care will be allowed except changes in dopamine replacement medications and interventions targeting specifically fine motor skills.

### {33} Plans for collection, laboratory evaluation, and storage of biological specimens for genetic or molecular analysis in this trial/future use

N/A

### {12} Outcomes

Primary mechanistic outcome for this study will be neurophysiology. We aim to uncover the underlying pathways utilized by NMT in the PD brain. Neurophysiologic data will be collected via MEG before and after any therapy or twice separated by a five week interval. We will be using a whole head neuromagnetometer (4D Neuroimaging) with an array of 248 sensors at a 678.17 Hz sampling rate and an acquisition bandwidth of 0.1–200 Hz during an auditory-motor task. Participants will be presented with 6 sequences of 30 ms acoustic burst stimuli (2000 Hz, intensity of 70 dB above subjective threshold) presented at 1 Hz. Each sequence will last 30 s with a 5-s break (180 total stimuli). They will be asked to tap their dominant index finger with the stimuli. After MEG data cleaning and preprocessing, time-frequency transformation and source localization will allow to measure relative beta and gamma oscillatory power in our regions of interest. We will evaluate group changes in directional functional connectivity between auditory, motor, and other regions of interest in the frequency domain using Granger causality.

Our primary motor outcome for this study will be finger dexterity. Similarly to our mechanistic outcome, will record changes in the total score on the Grooved Pegboard Test (GPT), which is a manipulative dexterity test consisting of 25 holes with randomly positioned slots [24] commonly used as a test of fine motor performance [25]. As the pegs must be rotated into position to be successfully placed, the GPT adds a dimension of complexity not found in other motor tasks and thus has been found to be a sensitive instrument in detecting general slowing due to medication or disease progression. In PD, the Grooved Pegboard Test has also been used extensively for identifying lateralized impairment [26] and as a motor outcome of clinical trials [27]. The time taken to complete the GPT with each hand is the score to be used in this application. Reliability for the test is good. Secondary motor outcomes designated for this study also assess fine motor abilities and will include the score on the finger-thumb opposition assessment (derived from the Neurological Evaluation Scale [28];) and the score from the finger tapping test on the UPDRS part III.

Quality of life (QOL) outcome measures will include the 39-Item Parkinson's Disease Questionnaire (PDQ-39) [22] and the Clinical Global Impression—Improvement Scale (CGI-I) to better define meaningful self-report and clinical changes. As an exploratory QOL outcome, we will include the Hospital Anxiety and Depression Scale (HADS) [29, 30] to assess for potential improvements in depressive symptoms and anxiety, which may improve with fine motor therapies.

### {18a-b, 19, 29} Data collection, management, and accessibility

MEG data collection is under the responsibility of a trained neurophysiology specialist to ensure data quality and assessment of unplanned data contamination. Motor scales and surveys are being collected by the study investigator who has been thoroughly trained by clinical and research colleagues during past clinical trials. Each measure and scale used in this study is widely used in the research community and has proven reliability and validity in the scientific literature. After collection, data is entered into the local Research Electronic Data Capture (REDCap) database, and data entry is verified by a research assistant non-affiliated to the study. Only complete sets of data (pre/post) will be included in the analysis. Study PI and statistician will have access to the final trial dataset.

### {14, 20a-c} Statistical methods and sample size

To address our primary mechanistic question, group comparison of mean Granger spectra changes using a linear mixed model controlling for sex and age will be analyzed during cued rhythmic tapping between regions of interest (ROIs: auditory, motor, precuneus, supramarginal gyrus and others) and corrected for multiple comparisons using the FDR method on the overall set of comparisons, *q* < 0.1. Statistically significant changes in Granger causality between ROIs are expected in the TIMP-RHY group but not in the OT or TIMP-NR groups due to the reliance on other motor networks, specifically those affected by PD pathology during fine motor training. A sample size per group of 25 subjects will allow us to determine between group differences with an effect size of 0.8 standard deviations/mean with 80% power and 0.05 significance, which is comparable to other studies examining neurophysiologic mechanisms of therapeutic interventions [31, 32] including similar studies using Granger causality as main outcomes in PD [33, 34]. We will perform exploratory analyses using linear regression to determine if any particular Granger feature is (1) associated with sex, age, or disease duration or severity and (2) more or less prone to motor function benefits. Based on our hypothesis, we predict fine motor training during TIMP-RHY, TIMP-NR, and OT will increase cortical motor beta and normalize gamma oscillations during the auditory-motor task in the MEG, although changes are expected to be stronger in the TIMP-RHY than in the OT and TIMP-NR groups. A 3 × 2 (group by frequency) mixed model ANOVA will be assessed to test this prediction.

We will address our clinical research question by determining whether there is a significant change in fine motor skills following TIMP-RHY, TIMP-NR, and OT due to fine motor training compared to the non-therapy condition. We predict that TIMP-RHY will decrease mean GPT scores to a higher extent than the TIMP-NR and the OT groups. We will use an ANOVA F-test model to test this prediction on the mean GPT score change as well as pairwise contrasts with Tukey-Kramer correction for multiple comparisons to assess where the differences are. We do not expect such changes in the waitlist group due to the absence of fine motor strengthening. Given the large effect size of 0.8 sd/mean seen in other PD studies using the GPT grooved pegboard test as main outcome [35, 36], we anticipate that our sample size of 25 per group will allow us to determine a group difference of 15% decreased time using the dominant hand and to be comparable to published data [37]. We will also perform exploratory analyses using regression modeling to assess whether (1) sex, age, or disease severity and (2) cortical motor beta power changes are correlated with fine motor tests performance.

We will address our QOL research question by assessing changes in the PDQ-39 and CGI-I scales. As fine motor skills may improve, we expect a decrease in mean total scores (the higher the scores the higher the problems with quality of life, depression/anxiety and how things have changed) after a 5-week TIMP-RHY session and to a lower extent after OT or TIMP-NR sessions. We do not expect a change of QOL mean scores in the waitlist group.

Only complete sets of data (including both pre and post) will be included in the analysis. No imputation or other methods for handling missing data will be used during the analysis process.

No interim or subgroup analyses will be performed.

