### {8 & 13} Trial design and timeline

After enrollment and screening assessment, 100 PD subjects will be randomly assigned (parallel assignment) in a 1:1:1:1 ratio to TIMP-RHY (25 people), or OT (25 people), or TIMP-NR (25 people) groups, or to wait for 5 weeks (Waitlist control group; 25 people). All PD subjects will undergo a magnetoencephalography (MEG) scan and a battery of tests before and after the TIMP-NR, TIMP-RHY, OT intervention, or twice separated by a 5-week period free of intervention (waitlist control group). First, to capture neural network and neurophysiological changes, participants will perform an MEG scan which engages them in an auditory-motor task. Then, clinical measures will be based on standardized PD neurologic assessments via the Unified Parkinson’s Disease Rating Scale [1], and fine motor assessments will include the Grooved Pegboard Test and finger-thumb opposition tests. Last, to capture changes in quality of life (QOL), we have included the 39-Item Parkinson's Disease Questionnaire (PDQ-39) [22]. The total duration of participation is 5–7 weeks (see the study flowchart in Fig. 1).

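### The primary mechanistic model compares change in Granger spectra adjusted for sex and age but not for the baseline Granger value, so a valid analysis gives up precision that the trial already has the data to recover

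*Protocol article*

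**What the plan says.** The section on statistical methods and sample size ({14, 20a-c}) sets the primary mechanistic analysis as a "group comparison of mean Granger spectra changes using a linear mixed model controlling for sex and age". Results across regions of interest are then "corrected for multiple comparisons using the FDR method on the overall set of comparisons", at q < 0.1. The response is therefore the change between scans, and the named adjustment variables are sex and age. No other section adds the baseline Granger value.

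That value is available. Under Outcomes ({12}): "Neurophysiologic data will be collected via MEG before and after any therapy or twice separated by a five week interval". Under data collection ({18a-b, 19, 29}): "Only complete sets of data (pre/post) will be included in the analysis". The statistical section repeats the complete-pairs rule and rules out imputation.

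On size, the same section states: "A sample size per group of 25 subjects will allow us to determine between group differences", with "an effect size of 0.8 standard deviations/mean" and "with 80% power and 0.05 significance". Under trial design ({8 & 13}), "100 PD subjects will be randomly assigned (parallel assignment) in a 1:1:1:1 ratio". The randomisation section ({16a-c}) describes a random number sequence and no stratification. It also says that participants learn their assignment once their first research visit has been scheduled, and so before that visit takes place.

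**The concern.** A change score subtracts the whole of the first scan from the second, which fixes the slope on baseline at 1. With equal variances at the two scans, the slope that the data support is rho. Unless rho is close to 1, the raw change carries more of the first scan's noise than it needs to. An arm that by chance starts low on a connection will also tend to rise on rescanning. Adjusting for sex and age does not remove this, except so far as those two predict baseline connectivity.

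The mixed-model label does not settle the matter. On complete pairs, a group-by-time model with a free baseline mean in each arm returns the same contrast as the change score.

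At stake is the precision of each between-arm contrast in Granger change. The mechanistic hypothesis rests on those contrasts, since the protocol expects change with TIMP-RHY but not with OT or TIMP-NR.

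**Working it through.** **Inputs from the protocol article.** 25 per arm; effect 0.8 SD; 80% power; significance 0.05 (sidedness not stated; two-sided reproduces the plan); covariates sex and age.

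**Assumptions not in the document.** Pre/post correlation rho, shown over a range; equal variance at the two scans; 0.8 taken as SDs of the change score, the variable analysed. A second reading of the 0.8 is checked in step 4.

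**1. The plan's own figure.** n per arm = 2(1.960 + 0.842)² / 0.8² = 2 × 7.85 / 0.64 = 24.5, so 25. Power at n = 25 is 80.7% by the normal approximation. By the noncentral t, the noncentrality is 0.8 × √(25/2) = 2.83. Power is then 79.1% with 46 error df (two arms, sex and age) and 79.9% with 94 df (all four arms in one model). The stated 80% reproduces.

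**2. Effect of adding baseline.** With a common variance σ², the change has variance 2σ²(1 − rho). The residual after baseline adjustment has variance σ²(1 − rho²). The ratio is (1 + rho)/2, so the effective standardised effect is 0.8 / √((1 + rho)/2). Noncentral t with 45 df, two-sided 0.05, one contrast:

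| rho | variance ratio | effective effect | power without baseline | power with baseline | gain (points) |
|---|---|---|---|---|---|
| 0.3 | 0.65 | 0.992 | 79.1% | 93.0% | 14 |
| 0.5 | 0.75 | 0.924 | 79.1% | 89.2% | 10 |
| 0.7 | 0.85 | 0.868 | 79.1% | 85.1% | 6 |
| 0.8 | 0.90 | 0.843 | 79.1% | 83.1% | 4 |
| 0.9 | 0.95 | 0.821 | 79.1% | 81.0% | 2 |

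With four-arm error df the comparison at rho 0.5 is 79.9% against 89.8%. A simulation of two arms of 25 (8,000 trials, without sex and age) gave 79.5% against 88.8% at rho 0.5, and 79.6% against 82.2% at rho 0.8.

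**3. Chance baseline difference.** The difference in baseline means between two arms of 25 has SD √(2/25) = 0.28 baseline SDs. The change contrast moves by −(1 − rho) per unit of that difference. A one-SD chance difference therefore shifts it by 0.20, 0.14, 0.08, 0.06 or 0.03 SD at rho 0.3, 0.5, 0.7, 0.8 or 0.9. In the simulation at rho 0.5 the slope was −0.48, and the correlation between the unadjusted contrast and the baseline difference was −0.48. For the adjusted contrast that correlation was 0.01.

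**4. If the 0.8 is in single-scan SDs.** The effective effects become 0.8 / √(2(1 − rho)) without baseline and 0.8 / √(1 − rho²) with it:

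| rho | without baseline | with baseline |
|---|---|---|
| 0.3 | 65% | 83% |
| 0.5 | 79% | 89% |
| 0.7 | 94.7% | 97.2% |
| 0.8 | 99.2% | 99.6% |

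The two readings agree at rho 0.5, where the change SD equals the single-scan SD. On the single-scan reading the gain is larger at low rho and smaller at high rho.

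**The case against.** The strongest reply is that nothing is broken. In a randomised comparison the change-score contrast is unbiased, its standard error already allows for chance baseline differences, and its error rate is nominal. The stated power is met without any change. All of this stands. A reader might infer that the plan will mistake regression to the mean for a therapy effect, or that the trial is underpowered. The document supports neither. What remains is lost precision, and sensitivity to whatever imbalance occurs in the one trial that is run.

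Second, the size rests on inputs that the document does not give: no pre/post correlation for Granger measures, and no clear scale for the 0.8. This also stands, and it is why a range is shown. A reader might also infer that the FDR step makes the loss worse. That is not shown: the plan sets q < 0.1 and no per-connection significance level, and a step-up cut-off depends on the data.

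Third, the article is condensed, and an unseen analysis plan might add the term. This carries less weight. The sentence names the response, the model and the adjustment variables, so it states a choice. It does not say that sex and age are the only covariates, but an analysis plan that follows it as written would leave baseline out.

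Fourth, participants learn their arm before the first research visit, so the baseline scan is not strictly a pre-assignment measurement. This stands against one remedy: a longitudinal model that forces a common baseline mean across arms relies on an equality that this timing makes less secure. Covariate adjustment does not impose that equality, and the planned change score uses the same first scan.

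**Conclusion.** The point holds as one about efficiency, not validity. The primary mechanistic model leaves out a covariate that every analysed participant has and that is measured on the same scale as the outcome. With equal variances, 25 per arm, 0.8 SD of the change and one two-sided contrast at 0.05, adding it raises power by about 14 points at rho 0.3, 10 at 0.5, 6 at 0.7, 4 at 0.8 and 2 at 0.9. It also removes the linear dependence of the contrast on chance baseline differences. No single figure can be claimed, because rho is unknown. If the 0.8 refers to single-scan SDs, the gain is about 2.5 points at rho 0.7 and under 1 point at 0.8. The change is worth making because it costs so little, not because the planned analysis would mislead.

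**What to change.** In the section on statistical methods and sample size, add the baseline Granger value of the same connection as a covariate beside sex and age in the primary mechanistic model. The response may be the post-intervention value or the change; with baseline in the model, the group contrast is the same. Keep the planned FDR step. Make the amendment before group results are examined.

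Do not substitute a model that constrains the arms to a common baseline mean, given when participants learn their assignment.

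The cost is one sentence, one degree of freedom and an assumed linear baseline slope per connection. No new data, visits or participants are needed, and no one drops out of the analysis, because complete pairs are already required.

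### The 80% power for the primary mechanistic outcome belongs to one unadjusted test at 0.05, not to the planned set of Granger comparisons under FDR q < 0.1

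*Protocol article*

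**What the plan says.** The Outcomes section ({12}) of the protocol article introduces the endpoint with "Primary mechanistic outcome for this study will be neurophysiology" and plans to evaluate group changes in "directional functional connectivity between auditory, motor, and other regions of interest in the frequency domain using Granger causality".

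The section on statistical methods and sample size ({14, 20a-c}) sets the analysis as a "group comparison of mean Granger spectra changes using a linear mixed model controlling for sex and age". The regions are listed as "ROIs: auditory, motor, precuneus, supramarginal gyrus and others". Results are to be "corrected for multiple comparisons using the FDR method on the overall set of comparisons", at q < 0.1.

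A little further on in the same paragraph, 25 per group is said to allow detection of between-group differences with an "effect size of 0.8 standard deviations/mean with 80% power and 0.05 significance". That sentence mentions neither the FDR rule, nor the number of comparisons, nor which of the possible group contrasts it refers to. The Granger analysis has no connection, direction or group contrast marked as primary.

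**The concern.** A power figure describes a decision rule. Here the paragraph contains two: significance at 0.05, used to justify the sample size, and FDR q < 0.1 over a whole set of comparisons, used to analyse the data. The power is quoted for the first and the data will be judged by the second.

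Under an FDR step-up rule, the p-value needed for one connection depends on how many comparisons are in the set and how many of the others are also small. If few connections change, the effective threshold is far stricter than 0.05. If nearly all change, it approaches 0.1. A single 80% cannot describe this.

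The mechanism of the intervention is part of the trial's central goal. A reader who trusts the 80% would take a non-significant auditory-motor connection as fair evidence against the hypothesis, when the chance of detecting a true 0.8 SD change there might have been nearer one half or lower.

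**Working it through.** **Inputs from the protocol article.** 25 per group; effect size 0.8; significance 0.05; power 80%; FDR q = 0.1; four named regions.

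**Assumptions, because the text does not say.** The effect size is read as a standardised difference of 0.8 SD. Tests are two-sided. The FDR method is Benjamini-Hochberg. Each comparison is treated as a two-group t-test with 25 + 25 − 2 = 48 degrees of freedom, and tests are independent unless noted.

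**Step 1: reproduce the stated figure.**
- Normal approximation: n = 2 × (1.96 + 0.84)² / 0.8² = 24.5, so 25 per group.
- Noncentrality with 25 per group: 0.8 × √(25/2) = 2.83. Normal power is Φ(2.83 − 1.96) = 0.81; noncentral t power is 0.79.
- A one-sided test would need only 20 per group, so two-sided is the reading that fits.

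The arithmetic is sound for one unadjusted two-group comparison.

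**Step 2: thresholds under the planned rule.** With m comparisons, Benjamini-Hochberg rejects the k smallest p-values, where k is the largest rank whose p-value is at most 0.1 × k/m. Four regions give 4 × 3 = 12 directed pairs, hence m = 12 for one group contrast.
- Strictest threshold (k = 1): 0.1/12 = 0.0083; power 0.53.
- Threshold equal to 0.05: requires 0.1 × k/12 = 0.05, so k = 6. The planned rule works at 0.05 only when half of the set is declared significant.
- Most lenient threshold (k = 12): 0.1; power 0.87.

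**Step 3: power per true connection, by simulation** (Benjamini-Hochberg at q = 0.1, 25 per group, true effects 0.8 SD; Monte Carlo error below about 0.01).

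| Comparisons m | Truly different | Power per true connection |
|---|---|---|
| 12 | 1 | 0.56 |
| 12 | 3 | 0.67 |
| 12 | 6 | 0.77 |
| 12 | 12 | 0.86 |
| 24 | 1 | 0.46 |
| 72 | 1 | 0.32 |

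The sets of 24 and 72 are illustrations: 12 directed pairs with 2 contrasts, and 12 directed pairs with 6 contrasts (or 3 contrasts in 2 bands). With a correlation of 0.3 between tests, the first row becomes 0.55.

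**Step 4: scale.** At the strictest threshold, 80% power for 0.8 SD would need about 40 per group with m = 12 and about 54 with m = 72, against the planned 25. This shows the distance between the two rules; it is not a proposal to enlarge the trial.

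**The case against.** **The size of the set is not in the text.** This is correct. The model can be read as one overall group test per connection. Beta and gamma are attached to oscillatory power and to a separate group-by-frequency ANOVA, not clearly to the Granger analysis. The stated expectation sets TIMP-RHY against OT and TIMP-NR, not every pair of arms. Any set larger than 12 is therefore an assumption. Under the reading with one overall group test per connection and a shift in TIMP-RHY only, simulated power with 12 connections is 0.61, 0.71, 0.81 and 0.88 for 1, 3, 6 and 12 true connections. That is somewhat better, but again a range and not 80%.

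**The loss of power is not certain.** A reader might infer that the auditory-motor connection must have far less than 80% power. The documents do not support that. The hypothesis concerns compensatory networks, which suggests that several connections change, and if nearly all do, power exceeds 80%.

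**The error rate is disclosed.** A reader might also infer that the plan promises a 5% false-positive rate and delivers 10%. It does not: 0.05 appears only as an input to the power statement, and q < 0.1 is openly declared for the analysis. Choosing that q for a mechanistic outcome is the sponsor's decision.

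**The open list of regions may be mere condensation.** An article can leave the full list to the complete protocol or SAP, so the open list alone is no fault. Nor does anything in the document say that regions will be chosen after seeing results; the statistician is described as blinded. A reader should not infer post hoc selection.

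**What stands after all this.** The power sentence and the FDR sentence are both in the published paragraph and describe different analyses. An SAP that lists every region would not make the first describe the second.

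**Conclusion.** The stated power is wrong for the analysis it is meant to support. The 80% holds for one unadjusted two-group comparison at two-sided 0.05 (0.79 by the t distribution, with 25 complete pre/post pairs in each group). It is not a property of the planned FDR analysis. With 12 comparisons, power per true connection lies between about 0.56 and 0.86, depending on how many connections change. With one true connection it drops further as the set grows. The 80% is too high unless most connections change.

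These figures rest on independent t-tests, Benjamini-Hochberg and true differences of exactly 0.8 SD. Age and sex adjustment, the mixed model and correlation between connections would move them, but would not turn the range into a single 80%. The finding is limited to this mismatch; it does not say that FDR control, q < 0.1 or a multi-connection primary question is inappropriate.

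**What to change.** Before the MEG data are analysed, do one of the following.

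(a) Keep the multi-connection primary analysis. Fix the list of regions, directions, any frequency bands and group contrasts, state the resulting number of comparisons, and replace the 80% with a range of power under FDR q < 0.1 for stated numbers of true effects.

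(b) Have the sponsor pre-name one primary connection and one group contrast, tested two-sided at 0.05, to which the existing 80% applies. Report the other connections as secondary under FDR q < 0.1 with no power claim. Which connection, which band (if one is used) and which comparator is the sponsor's scientific choice.

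Either option changes only the protocol and SAP wording and needs no further participants or measurements. Option (a) means publishing a less reassuring power statement. Option (b) moves the wider network question to secondary status.

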**Methods:**

One hundred PD participants will be randomly assigned to receive 15 sessions of either TIMP with rhythm or TIMP without rhythm, standard of care OT, or to be waitlisted (control) over 5 consecutive weeks. Brain oscillatory responses will be collected using magnetoencephalography during an auditory-motor task to understand the underlying mechanisms. The Grooved Pegboard, the UPDRS III finger tap, and the finger-thumb opposition will be assessed to investigate clinical changes related to fine motor function. This project will also serve to confirm or refute our pilot data findings suggesting NMT relies on compensatory brain networks utilized by the PD brain to bypass the dysfunctional basal ganglia.

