### {6b & 7} Research objectives and comparators

The central goal for this study is to investigate the underlying networks used during TIMP and test the rehabilitative power of TIMP techniques for fine motor control in PD. Specifically, the study aims to demonstrate whether the use of musical instruments to specifically promote fine motor function allows differential mobilization of neuronal networks when they are combined with external rhythmic cueing. To allow for an accurate clinical comparator, a standardized OT research protocol will be tested as well.

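### The rhythm hypothesis is worded as significant Granger change in TIMP-RHY and not in OT or TIMP-NR, and is tied to no direct contrast between arms

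*Protocol article*

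**What the plan says.** The aim is a difference between arms. The research objectives (protocol article, {6b & 7}) ask whether using musical instruments "allows differential mobilization of neuronal networks when they are combined with external rhythmic cueing".

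The statistical section ({14, 20a-c}) names a matching analysis: "group comparison of mean Granger spectra changes using a linear mixed model controlling for sex and age", "corrected for multiple comparisons using the FDR method on the overall set of comparisons", with q below 0.1. The sample size is also stated between groups: "A sample size per group of 25 subjects will allow us to determine between group differences with an effect size of 0.8 standard deviations/mean". The power is put at 80% and the significance level at 0.05.

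Between these two statements stands the expected result: "Statistically significant changes in Granger causality between ROIs are expected in the TIMP-RHY group but not in the OT or TIMP-NR groups". The protocol gives a biological reason for the expected absence, namely that training in those two arms relies on motor networks damaged by the disease.

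The section words its other predictions as comparisons. Beta and gamma changes are expected to be stronger in TIMP-RHY than in the other two therapy arms, tested by a group-by-frequency mixed ANOVA. The Grooved Pegboard score is expected to fall further in TIMP-RHY, tested by an F-test with Tukey-Kramer pairwise contrasts. Only the Granger prediction is stated as significant in one arm and not in the others.

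**The concern.** A difference in significance is not a significant difference. Two arms can have the same true change and fall on opposite sides of the threshold. The second half of the prediction is the weaker one. With 25 people per arm, a non-significant result in OT or TIMP-NR may be a missed effect, yet the protocol already supplies a mechanism to explain it.

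Read as worded, the prediction can fail in both directions. Equal network changes under all three therapies could look specific to rhythm. A truly larger change in TIMP-RHY would contradict the prediction if OT or TIMP-NR also reached significance. The abstract says the project will "confirm or refute our pilot data findings suggesting NMT relies on compensatory brain networks utilized by the PD brain to bypass the dysfunctional basal ganglia", so how support is judged matters.

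Naming a group comparison does not settle this. A four-arm group effect could come from the waitlist arm alone. The rhythm claim needs TIMP-RHY set against TIMP-NR and against OT.

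**Working it through.** **Inputs from the protocol.** 25 per arm, 0.8 SD between groups (printed as standard deviations/mean and read here as SD), 80% power, significance level 0.05, FDR at 0.1. The regions are given as "ROIs: auditory, motor, precuneus, supramarginal gyrus and others".

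**Assumptions.** The within-arm effect is not given, so d = 0 to 0.8 SD of change is used. The four named regions give 4 × 3 = 12 directed connections; the open list may add more. All 25 per arm are analysed, which is the best case because only complete pre/post pairs are used.

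**1. The plan's own figure.** n = 2(1.960 + 0.842)² / 0.8² = 24.5, rounded up to 25 per arm. Power at 25 is 80.7% by the normal formula and 79.1% by the two-sample t-test. The stated sample size reproduces, for a single two-sided between-arm comparison.

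**2. One connection, identical true change in all three therapy arms.** Let p be the power of a within-arm paired t-test (noncentral t, 24 df, noncentrality 5d, two-sided 0.05). With independent arms, the chance that TIMP-RHY is significant and the other two are not is p(1 − p)².

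| d (SD) | p | p(1 − p)² |
|---|---|---|
| 0 | 5.0% | 4.5% |
| 0.2 | 16.1% | 11.3% |
| 0.3 | 30.2% | 14.7% |
| 0.4 | 48.4% | 12.9% |
| 0.5 | 67.0% | 7.3% |
| 0.6 | 82.1% | 2.6% |
| 0.8 | 97.0% | 0.1% |

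The expression peaks at p = 1/3, where it equals 4/27 = 14.8%. That ceiling holds for any threshold.

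**3. Direct tests on the same data (100,000 simulated trials per value of d).** A three-arm F-test rejects in about 5%. TIMP-RHY beats both comparators in about 0.5%. Among trials that show the pattern at d = 0.3 to 0.5, the F-test is significant in only about 6% to 8%.

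**4. If significance means change against waitlist.** With no change in waitlist and equal change in the three therapies, the pattern occurs in 7.2% (0.3 SD), 8.9% (0.5 SD) and 3.8% (0.8 SD) per connection. The problem does not depend on reading the sentence as within-arm tests.

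**5. At least one of 12 connections.** Without correction and with independent connections, 1 − (1 − 0.073)¹² = 60% at 0.5 SD. This is illustrative only, because the protocol applies FDR. With Benjamini-Hochberg at 0.1 over 3 × 12 = 36 within-arm tests, 6 or 12 connections truly changing equally in all arms, and between-connection correlation 0 or 0.5, simulation gives:

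| Common change (SD) | At least one connection with the pattern |
|---|---|
| none | 3–4% |
| 0.3 | 27–70% |
| 0.4 | 40–77% |
| 0.5 | 29–56% |
| 0.6 | 11–35% |
| 0.8 | 0.2–25% |

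At 0.8 SD the upper end comes almost wholly from connections with no true change that the FDR procedure lets through. Requiring TIMP-RHY to beat both comparators by FDR-corrected direct contrasts gives a false claim in about 1% to 2% of trials throughout.

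**6. Price in power.** At 0.5 SD, a within-arm test has 67% power and a two-sample contrast with 25 per arm has 41%, both unadjusted.

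**The case against.** The strongest reply is that the sentence is a prediction and not a decision rule. The sentence before it names a between-group model of change, and the sentence after it sizes the trial for between-group differences. Nowhere does the protocol plan separate within-arm tests or let three within-arm verdicts decide the hypothesis. All of this stands. A reader might infer that the primary mechanistic analysis is itself a comparison of within-arm significance; the documents do not support that.

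It can also be said that listing contrasts from a named model is commonly left to a statistical analysis plan or the full protocol. That is right, and the missing list alone would be no finding. What remains is what the text does say: the only stated pattern of support for the rhythm hypothesis on this outcome is an unsound one, while the neighbouring predictions are worded as comparisons.

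The size must not be overstated either. A reader might infer that the misleading pattern is frequent for any given connection. It is not: the ceiling is 14.8%, and it is rare when the common effect is large. The higher figures depend on an assumed number of connections, moderate common effects and a family of within-arm tests that the protocol does not plan.

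**Conclusion.** The concern holds as a fault in how the expected result is worded, not in the named test or the sample size, which reproduces. A significant change in TIMP-RHY beside non-significant changes in OT and TIMP-NR would not show that rhythm mobilises different networks.

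Under identical effects the pattern has at most about a 15% chance per connection: 7% at 0.5 SD and about 0.1% at 0.8 SD. Across 12 assumed connections with a common change of 0.3 to 0.5 SD under FDR control, at least one shows it in roughly 25% to 70% of trials (one extreme case reached 77%), against about 1% to 2% for direct contrasts. With no change anywhere the figure is only 3% to 4%. The word often is therefore fair only across many connections with moderate common effects. Effect size, number of connections and correlation are all assumptions, since the protocol gives none of them.

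**What to change.** In the statistical section, replace the sentence with one to this effect: a larger Granger change is expected in TIMP-RHY than in TIMP-NR and than in OT, and this is judged by the contrasts TIMP-RHY minus TIMP-NR and TIMP-RHY minus OT from the linear mixed model, FDR-corrected. Add that within-arm changes are reported as estimates with 95% confidence intervals and do not serve as evidence of rhythm specificity, and that non-significance in OT or TIMP-NR is not read as absence of change. No equivalence margin is needed, provided no claim of absence is made.

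The change is one of wording, because the planned model already yields both contrasts. The cost is power. At 0.5 SD a direct contrast has about 41% power against 67% for a within-arm test, before adjustment. At the planned 0.8 SD a single contrast keeps about 79%; as a guide to the effect of multiplicity, a Bonferroni split over three contrasts would leave about 64%. Some results will have to be reported as inconclusive.
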